**Discussion:**

UROPOT tests a novel antimicrobial strategy based on “metabolic potentiation” for prophylaxis enabling aminoglycoside dose reduction and targeting biofilm activity. The anti-biofilm effect may prove beneficial, particularly in patients who have a permanent stent in situ needing recurrent endourological manipulations strategies in preventing infections and achieving sustained microbiological eradication in pre-stented patients.

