### Participants/eligibility criteria

Patients with asymptomatic *E. coli* and/or *K. pneumoniae* bacteriuria, undergoing endourological procedures. Inclusion and exclusion criteria determining the eligibility of study participants are reported in Table 1. Bacteriuria is defined as ≥ 10^2^ CFU/ml for both *E. coli* and *K. pneumoniae*. In case of mixed cultures, *E. coli* and/or *K. pneumoniae* should be significantly more enriched than other bacteria (i.e., ratios of quantitative results in CFU/ml of *E. coli*/other bacteria or *K. pneumoniae*/other bacteria are > 100).

**Table 1 Tab1:** Inclusion and exclusion criteria of the UROPOT trial

Participants fulfilling all the following inclusion criteria are eligible for the study:
1. Written informed consent
2. Adults (≥18 years)
3. Patients with a ureteral stent in situ
4. Patients scheduled for endourological ureteral manipulations (e.g. endourological stone surgery, ureteral stent exchange)
5. Asymptomatic bacteriuria with strains of E. coli and/or K. pneumoniae sensitive to ceftriaxone and amikacin.
The presence of any one of the following exclusion criteria will lead to exclusion of the participant:
1. Allergy to one of the study drugs or excipients (Beta-lactams, aminoglycosides or mannitol)
2. Pregnant and lactating women
3. Glomerular filtration rate (CKD-EPI eGFR) < 50ml/min / 1,73m2
4. Middle to severe hearing impairment
5. Myasthenia gravis or other forms of myoneural disorders
6. Congestive heart failure, pulmonary oedema
7. Intracranial haemorrhage, compromised blood-brain barrier
8. Antibiotic treatment within 14 days prior to randomization
9. Mixed cultures of E. coli and/or K. pneumonia with other bacteria
10. Previous (within 3 months prior to randomization) or concomitant participation in another interventional clinical trial
11. Inability to understand and follow the protocol
12. Inability to give informed consent

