### Study endpoints

The primary outcome is the rate of postoperative infections 48 h postoperatively. Postoperative infections include systemic symptoms and positive urine/blood cultures matching preoperative urine cultures as deemed by the adjudication committee. Secondary outcomes include microbiological eradication via anti-biofilm activity assessed through catheter sonication, quantitative culture, and intraoperative urine culture; sustained microbiological eradication measured by urine cultures at postoperative days 2 and 14; and primary pharmacokinetic parameters of mannitol and antibiotics in blood and urine samples at specified time points. Safety outcomes will include monitoring the incidence of adverse events related to amikacin/mannitol combination therapy throughout the study, including serious adverse events (SAEs) and pre-specified adverse events of special interest such as ototoxicity and nephrotoxicity, along with vital signs. Additionally, postoperative complications at day 14 will be assessed using the Clavien-Dindo classification [19].

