### Study procedures/participant timeline (Table 2)

During the screening visit (V0), patients with ureteral stents planned for endourological manipulation are preselected based on chart reviews every 2–4 weeks. A urine culture is taken as part of standard care. Written informed consent is obtained after a minimum 24-h reflection period, either on the day of intervention (for day-surgery) or the day before surgical intervention for pre-hospitalization, with results documented in both a screening log and the (eCRF). During visit 1 (V1), patients consenting to the study will undergo eligibility assessment by the investigator, followed by randomization conducted by pharmacy research staff. Data collected during the visit will be recorded in the eCRF, and patients will receive study treatment from the pharmacy as a single infusion bag, administered within 30 min of delivery, with intraoperative urine cultures and hardware extraction for culture, along with blood and urine samples for pharmacokinetic and antibiotic concentration quantitation. During visit 2 (V2), occurring 2 days post-intervention, patient history will be obtained regarding infectious complications; adverse events will be assessed and managed. Urine cultures and samples for antibiotic and mannitol analysis will be obtained, along with blood for safety laboratory assessments including electrolytes and creatinine, with all data recorded in the eCRF by research staff. During the end of study visit (V3), occurring 14 days post-intervention, patient history will be obtained regarding infectious complications, and adverse events will be assessed and managed. Urine cultures will be obtained, and blood may be drawn for safety laboratory assessments if deemed necessary based on pathological results from V2, with all data recorded in the eCRF by research staff.

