### Assignment of intervention

#### Blinding protocol

The study drugs will be prepared by the unblinded pharmacist investigators of the CHUV Pharmacy. The allocation sequence will be accessible through an interactive web response service (IWRS) embedded in the electronic case report form (eCRF9 (secuTrial®)), utilizing a pre-defined allocation table (block randomization) to ensure allocation concealment. Patients will be entered into the eCRF by the primary research team and transmitted to the pharmacy for randomization, with treatment prepared according to randomization and handed blindly to the research team. The randomization code will remain blinded to anyone involved in the study until the database is locked, and the allocation group will not be visible or accessible to assessors or patients throughout the study.

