### Statistical analysis

The primary outcome is the proportion of postoperative infections within 48 h postoperatively. Fisher’s exact test will applied to compare the proportions between mannitol + low-dose amikacin arm vs full-dose amikacin arm and mannitol + low-dose amikacin arm vs ceftriaxone arm, respectively. To account for multiple comparisons, single-step method will be applied to control the family-wise error rate. Odds ratios with 95% confidence intervals and associated *p* value will be reported. Due to its exploratory nature and limited number of participants, no interim analysis will be performed. Microbiological eradication will be compared between the same groups mentioned in the primary analysis using *t*-tests. Difference in means with 95% confidence intervals and *p* values will be reported. If normality assumption is not met and the data approximately follow a log-normal distribution, data will be log-transformed before applying *t*-tests. In this case ratios of geometric means with 95% confidence intervals and *p* value will be reported. If none of the above methods hold, non-parametric methods will be considered.

Sustained microbiological eradication will be analyzed using mixed-effects models to account for the repeated measurements. Fixed effects will be the baseline microbiological eradication measured at D0, the intervention, the visit (D2 and D14), and the interaction between the intervention and the visit. Subject-specific random effect will be considered. Statistical assumptions will be assessed, and a similar methodology will be applied as for microbiological eradication to addressed them.

Primary pharmacokinetic parameters in blood (Cmax, AUC, t1/2) will be calculated for mannitol, amikacin, ceftriaxone, and for each intervention arm. In urine, descriptive statistics will be reported without any specific comparisons and spot urine concentrations.

Planned analyses will adhere to the sections detailing primary, secondary, and safety analyses, with a statistical analysis plan finalized and signed by all parties before code break. Datasets for analysis include the intention-to-treat (ITT), per-protocol (PP), and safety populations, with primary and secondary outcomes assessed in the ITT population and safety outcomes analyzed in the safety population.

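### The model for sustained eradication at days 2 and 14 has no term for planned procedure or stent status, which costs some precision on a secondary endpoint

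*Protocol article*

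**What the plan says.** All passages are in the protocol article.

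- **Entry.** Table 1 requires "Patients with a ureteral stent in situ" (criterion 3) and admits "Patients scheduled for endourological ureteral manipulations (e.g. endourological stone surgery, ureteral stent exchange" (criterion 4). The two procedures are given as examples.
- **Day 0.** The participant timeline describes visit 1 "with intraoperative urine cultures and hardware extraction for culture", with no distinction by arm.
- **Endpoints.** Study endpoints lists two separate microbiological outcomes: "microbiological eradication via anti-biofilm activity assessed through catheter sonication, quantitative culture, and intraoperative urine culture", and "sustained microbiological eradication measured by urine cultures at postoperative days 2 and 14".
- **Model.** Statistical analysis specifies a mixed-effects model for the second of these: "Fixed effects will be the baseline microbiological eradication measured at D0, the intervention, the visit (D2 and D14), and the interaction" of intervention with visit, plus a subject-level random effect.
- **Allocation.** The Blinding protocol describes an allocation system "utilizing a pre-defined allocation table (block randomization) to ensure allocation concealment". It names no stratification factor.
- **Rationale.** Background and rationale describes stents as prone to colonisation, and that colonisation as the route to biofilm and asymptomatic bacteriuria. The Abstract's Discussion speaks of possible benefit "in preventing infections and achieving sustained microbiological eradication in pre-stented patients", and singles out those with a permanent stent.
- **Follow-up.** Table 2 schedules a stent discomfort questionnaire at screening and again at visits 2 and 3.

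**The concern.** By the time of the day 2 and day 14 cultures, the colonised stent has left the patient in all three arms. What happens next depends on the procedure. A stent exchange leaves a new foreign body in place; stone surgery need not. If a stent in place favours bacteriuria, as the protocol's rationale suggests, planned procedure is a baseline factor that predicts this endpoint, and it is known before randomisation because a scheduled procedure is an entry criterion.

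The listed fixed effects leave it out. The day 0 covariate cannot stand in for it: the day 0 samples are the intraoperative urine and the extracted hardware, and neither shows whether a new stent was left.

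At stake is the precision of the arm comparisons. Variation due to stent status stays in the residual, and with 30 patients per arm the procedure mix can differ by chance. A pooled estimate also does not describe patients who keep a stent, the group that the Abstract's Discussion singles out.

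**Working it through.** **What can be reproduced.** The 30 per group was set on practical grounds. The protocol gives no effect size, standard deviation or power for this endpoint, so there is no figure to re-derive. The 8% loss is stated for the primary outcome; applied here it leaves 30 × 0.92 = 27.6 per arm.

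**Assumed, not in the protocol.** Share of patients without a stent afterwards, *s*: 50%, with a range of 20% to 70%. Overall eradication: 50%. Difference in eradication between stent-free and re-stented patients, *d*: 20, 35 or 50 points.

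**1. Chance imbalance (30 per arm).** The SD of the between-arm difference in stent-free share is √(2·s(1−s)/30). At s = 0.5 this is √(0.5/30) = 0.129, and 1.96 × 0.129 = 0.253, so the 95% range is about ±25 points. Over s = 20% to 70% the SD is 10 to 13 points. By exact binomial calculation, a gap of at least 20 points occurs in about 7% to 16% of single comparisons. By simulation, it occurs in at least one of the two planned comparisons in 13% to 26% of trials.

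**2. Bias.** Imbalance of this kind is random. In simulations with no drug effect and a stent effect of 1 or 2 within-group SDs, an unadjusted t-test at one time point rejected in 4.8% to 5.2% of runs. The arm comparison keeps its nominal error rate.

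**3. Precision on a binary scale.** The unadjusted 95% half-width is 1.96·√(2 × 0.25/30) = 25.3 points. At s = 0.5 stent status explains s(1−s)d²/0.25 = d² of the variance, so the adjusted half-width is 25.3·√(1−d²).

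| Stent effect *d* | Variance explained | Shift from a 95% imbalance (0.253·d) | Adjusted half-width | Narrowing |
|---|---|---|---|---|
| 20 points | 4% | ±5.1 points | 24.8 | 2% |
| 35 points | 12% | ±8.9 points | 23.7 | 6% |
| 50 points | 25% | ±12.7 points | 21.9 | 13% |

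The shift in the third column is already part of the unadjusted interval. For d = 35 points, √(25.3² − 23.7²) = 8.9. It is not an extra error on top of it.

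**4. Precision on a means scale.** The protocol records CFU counts and plans comparisons of means or geometric means, so a continuous version is closer to the plan. Let the within-group SD be 1, the stent effect *g* SDs, the drug effect 0.75 SD (assumed), with 28 per arm and s = 0.5. The unadjusted SD is √(1 + 0.25g²).

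| *g* | Unadjusted SD | Variance explained | Power without the term | Power with the term |
|---|---|---|---|---|
| 0.5 | 1.03 | 6% | 78% | 80% |
| 1 | 1.12 | 20% | 71% | 80% |
| 1.5 | 1.25 | 36% | 61% | 80% |
| 2 | 1.41 | 50% | 51% | 80% |

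Both calculations use a single time point and ignore the day 0 covariate, the repeated measures and the small cost of estimating one more coefficient. That cost would eat into the 2% at the low end.

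**The case against.** The strongest reply is that the split between stent-free and re-stented patients is nowhere stated. The procedures are only examples, Table 2 labels the intervention as stent manipulation, and the stent questionnaire is scheduled at both follow-up visits without condition. All of this fits a trial in which most or all patients have a stent afterwards. If so, there is little for the term to explain. This stands, and it is why the size can only be given as a range.

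The rationale section also speaks of stents left for extended periods. It does not say that a fresh stent drives bacteriuria within 2 or 14 days. That stands too: the prognostic role is plausible, not shown.

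The unseen analysis plan could add covariates, and a condensed article may omit strata. So the protocol cannot be read as saying that randomisation is unstratified. Against this, the article does not leave the model open: it lists the fixed effects, and the list omits procedure.

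A reader might also infer that day 2 and day 14 urine is presented as a test of the removed stent's biofilm. Study endpoints does not do that; it keeps stent sonication and follow-up urine as separate outcomes. The remark on permanent-stent patients is discussion of possible benefit, not a planned inference from the pooled model.

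**Conclusion.** The point holds as a modest loss of precision. The fixed effects listed for sustained eradication omit a baseline factor that the protocol's own rationale makes plausibly prognostic and that is known before randomisation. Assuming an even split, 50% eradication overall and a 20 to 50 point stent effect, adjustment narrows the interval by about 2% to 13%. The gain would be larger with a strong effect on the count scale, and close to nil if nearly all patients are re-stented.

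A reader might go further and infer that the endpoint reflects stent status as much as the study drug, or that the arm comparison is biased. The documents support neither. They give no stent-free share, stent effect or drug effect; in the continuous calculation stent status reaches half of the outcome variance only with a 2 SD effect and an even split. Stent removal is common to all arms, and randomisation keeps the comparison unbiased.

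Severity: minor, for a secondary endpoint in an exploratory trial.

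**What to change.** Add planned procedure (stent exchange or planned re-stenting versus planned stent-free) as a fixed effect in the mixed model for sustained eradication. Take it from the surgical plan as recorded before randomisation. Report day 2 and day 14 results for the two groups descriptively; under an even split each would hold about 15 patients per arm, too few for separate tests. Record actual stent status after surgery and use it only in a sensitivity analysis, because it arises after randomisation.

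The cost is one degree of freedom, or two if the effect may differ by visit. Planned status may differ from actual status, which would weaken the adjustment without biasing it. The term can be written into the analysis plan, which the protocol says is signed before code break; if the list of fixed effects counts as protocol text, the change goes to the ethics committee and Swissmedic. Adding a randomisation stratum is not needed: the trial started on 15.02.2024, and changing the allocation while it runs would cost more than the covariate.

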Biofilm-associated bacteria exhibit “antibiotic tolerance,” and thus survive otherwise lethal doses of antibiotics, highlighting the need for effective strategies. While quinolones have an anti-biofilm activity, resistance in Enterobacteriaceae like *E. coli* or *K. pneumoniae* approaches 20% in Switzerland (*anresis.ch*), limiting their utility in urinary tract infection management. Addressing the lack of biofilm eradication strategies, rising antibiotic resistance, and the steady increase in endourological interventions following previous ureteral stenting, the UROPOT study aims to evaluate the clinical significance of a novel antimicrobial strategy during mucosal lesion-inducing procedures in pre-stented patients with asymptomatic bacteriuria.

Previous research in a murine catheter-associated urinary tract infection (CAUTI) model has demonstrated that metabolic stimulation by substrates such as mannitol can enhance the efficacy of aminoglycosides in killing *E. coli*, including tolerant forms like biofilms [13, 14]. Moreover, the potentiation allows a reduction of aminoglycoside dosing [15]. Amikacin and mannitol are both approved for clinical use but exhibit differing safety profiles. Aminoglycosides such as amikacin can cause dose-dependent ototoxicity and nephrotoxicity [16]. In contrast, mannitol is used without major side effects and is not metabolized by host cells, being fully excreted by the kidneys. Pharmacological data suggest that low systemic doses of aminoglycosides achieve urine concentrations far exceeding the Clinical and Laboratory Standards Institute breakpoint for Enterobacteriaceae, and a single dose can sustain therapeutic levels against pathogens like *E. coli* for up to 3 days, making it a promising outpatient option [17, 18].

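### If day-2 and day-14 variances differ, the planned subject-random-effect model for sustained eradication miscalibrates the per-visit arm contrasts; visit-specific variances would prevent this at almost no cost

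*Protocol article*

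**What the plan says.** The Study endpoints section defines the outcome as "sustained microbiological eradication measured by urine cultures at postoperative days 2 and 14". Under Statistical analysis the article states: "Sustained microbiological eradication will be analyzed using mixed-effects models to account for the repeated measurements". The fixed effects are the day-0 baseline, "the intervention, the visit (D2 and D14), and the interaction between the intervention and the visit". The only term for within-patient dependence is given as "Subject-specific random effect will be considered". No residual variance structure is stated.

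On departures from assumptions the article says: "Statistical assumptions will be assessed, and a similar methodology will be applied as for microbiological eradication to addressed them". For microbiological eradication, that methodology is a log transformation if the data look log-normal, and after that: "If none of the above methods hold, non-parametric methods will be considered". Further detail is left to a later document, "with a statistical analysis plan finalized and signed by all parties before code break", which is not shown.

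**The concern.** Every fixed effect is listed, followed by one subject-level term in the singular. With one observation per patient at each of two visits, the ordinary reading is a random intercept plus a common residual variance, which is compound symmetry. That model pools the day-2 and day-14 variances and uses the average for the contrast at each visit.

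There is some reason to doubt equal variances. The Background and rationale section says of low-dose aminoglycosides that "a single dose can sustain therapeutic levels against pathogens like" *E. coli* for up to three days, and two of the three arms contain amikacin. Day 2 lies inside that window, so counts may sit near the no-growth floor; by day 14 regrowth could separate patients. The Study visits table fits this: urine drug levels are scheduled at Visit 2 but not at Visit 3.

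The stated remedies address the shape of the distribution. A log transformation leaves no-growth cultures at a single floor value while positive cultures spread over several logs, so it need not equalise the visits. If the variances do differ, the day-2 and day-14 arm contrasts carry wrong intervals, in opposite directions. The day-14 contrast is the one most naturally read as evidence of sustained eradication.

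**Working it through.** The protocol states no SD, variance, positivity rate or power for this outcome, so there is no figure of its own to reproduce. The check is conditional on assumed inputs.

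**Inputs.** From the article: 30 patients per arm, three arms, visits at days 2 and 14, and the fixed effects above. Assumed: random intercept with one residual variance, complete data, no true arm difference. Also assumed: log10 CFU is 0 if there is no growth and N(4.5, 1) if there is growth.

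**Step 1: general formula.** With balanced data the model SE of a two-arm contrast at either visit is sqrt(((v2 + v14)/2) × 2/n). The true SE at a visit is sqrt(v × 2/n), with v the variance at that visit. The ratio of model SE to true SE is therefore sqrt(((v2 + v14)/2)/v). Coverage is 2Φ(1.96 × ratio) − 1, and null rejection is one minus that. Let r = SD at day 14 / SD at day 2:

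| r | Day-2 coverage | Day-14 coverage |
|---|---|---|
| 0.5 | 87.9% | 99.8% |
| 0.8 | 92.4% | 97.3% |
| 1 | 95.0% | 95.0% |
| 1.25 | 97.3% | 92.4% |
| 1.5 | 98.8% | 90.4% |
| 2 | 99.8% | 87.9% |

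Mixed models fitted by REML to 300 simulated trials per setting (within-patient correlation 0.5 assumed) agree. Day-2/day-14 coverage was about 91%/100% at r = 0.5, 94%/95% at r = 1 and 99%/89% at r = 2. The model's SE was identical at the two visits every time (0.203, 0.259 and 0.411). The formula for r = 2 gives sqrt(2.5 × 2/30) = 0.408.

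**Step 2: assumed culture positivity.** For positivity p, the variance is v = p(1 + 4.5²) − (4.5p)² = 21.25p − 20.25p². At p = 5% this is 1.0625 − 0.0506 = 1.012; at 50% it is 10.625 − 5.0625 = 5.5625. The mean is 3.287. The day-14 SE ratio is sqrt(3.287/5.5625) = 0.769, so rejection is 2(1 − Φ(1.96 × 0.769)) = 13.2%. Other pairs in the same way:

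| Positive at day 2 / day 14 | v2 / v14 | Rejection at day 2 | Rejection at day 14 |
|---|---|---|---|
| 5% / 50% | 1.01 / 5.56 | 0.04% | 13.2% |
| 10% / 50% | 1.92 / 5.56 | 0.6% | 10.8% |
| 15% / 50% | 2.73 / 5.56 | 1.6% | 9.1% |
| 20% / 50% | 3.44 / 5.56 | 2.5% | 7.8% |
| 30% / 50% | 4.55 / 5.56 | 3.9% | 6.2% |
| 20% / 20% | 3.44 / 3.44 | 5.0% | 5.0% |
| 40% / 80% | 5.26 / 4.04 | 6.5% | 3.5% |
| 40% / 20% | 5.26 / 3.44 | 7.5% | 2.8% |

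Simulation with 20,000 trials per setting gives the same picture: 13.3%, 10.8% and 7.9% at day 14 for 5%, 10% and 20% at day 2. Simulation runs at these settings ranged up to about 14%. Fitted mixed models, 700 per setting, gave 11.6%, 9.6% and 9.9%. Their Monte Carlo error is about sqrt(0.1 × 0.9/700) = 1.1 percentage points, so they support the size but not a fine gradient. With visit-specific variances, rejection in the 20,000-trial runs was 4.1% to 4.9% at both visits in all six pairs simulated.

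**Step 3: which tests are affected.** With two visits and complete data, the visit-averaged arm effect rests on the variance of the patient's sum, and the interaction on the variance of the patient's difference. The random-intercept model estimates both without needing v2 = v14. In simulation at 5%/50% and 20%/50% these tests rejected about 5.0%. The miscalibration is confined to contrasts reported separately by visit.

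**The case against.** **The model is not fixed.** The article says only that a random effect will be considered. It names neither a random intercept nor a common residual variance, a subject effect can coexist with visit-specific residual variances, and covariance structure is usual analysis-plan content. This stands in part: the point cannot be called an error in the protocol. But the one dependence structure the text offers ordinarily means compound symmetry, and nothing in it points to visit-specific variances.

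**The direction is not documented.** A reader might infer that day-14 intervals will be too narrow and day-2 intervals too wide. The documents do not support that as fact. The three-day statement concerns aminoglycosides, not ceftriaxone, and says nothing about day 14. The Discussion section itself warns that exposure may be too short for the maximal effect, so near-zero day-2 counts cannot be presumed. The 40%/80% and 40%/20% rows show the reversal. This stands in full.

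**The harm depends on per-visit contrasts,** which the article does not explicitly name as the reported result. This stands. Still, an intervention-by-visit term is normally included so that arms can be compared at each visit.

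**The fallback might rescue the analysis.** Data with many zeros are neither normal nor log-normal, and a rank comparison at each visit pools no variance across visits. This stands in part. The fallback is only to be considered, is triggered by distributional shape rather than unequal variances, and is not said to be applied visit by visit.

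**Conclusion.** The point holds as a conditional improvement. On the ordinary reading, the model forces one variance on two visits that may well differ, and the listed remedies do not model that difference. Where variances differ, the per-visit intervals are wrong at both visits. Under 5% to 20% positivity at day 2 and 50% at day 14, nominal 5% rejection becomes about 8% to 14% at day 14 and 0% to 2.5% at day 2. At 30% against 50% it is only 6.2% at day 14, and at equal variances there is no error.

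These sizes rest on an assumed positivity pattern, an assumed count distribution, complete data and the random-intercept reading. A larger variance at day 14 is plausible from the protocol's rationale but is not established. The outcome is secondary and the trial exploratory, so the consequence is limited to how far the separate day-2 and day-14 comparisons can be trusted.

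**What to change.** In the analysis plan, before code break, replace the single subject random effect with a repeated-measures model. Keep the same fixed effects and use an unstructured 2x2 within-patient covariance: a day-2 variance, a day-14 variance and one covariance. Take the arm contrasts at each visit from that model. This corrects the calibration whichever visit is the more variable, so no one has to predict the ordering. It has three covariance parameters against two for a random intercept plus residual, which 90 patients with two visits can support. The likelihood-based handling of missing data is retained. Estimation method and degrees of freedom can stay with the analysis plan. The cost is one sentence of text and a minor change to the code.

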**Assessments:**						
Patient history, physical exam, pregnancy test		x				
Ureteral stent discomfort questionnaire		x			x	x
Vital signs (temperature, blood pressure, heart rate, and respiratory rate)		x		x	x	x
Blood draw for analyses: sodium, potassium, creatinine, eGFR (CKD-EPI), complete blood count		x^a^		x^b^	x	x^c^
Urine sampling for analyses: urine culture (microbiology)		x^a^		x^b^	x	x
**Assessment of anti-biofilm activity (secondary outcome)**				x		
Blood draw for analyses: aminoglycoside + mannitol level (AMK/Man level) at 1, 3, and 6 h after administration of drug				x		
Urine sampling for analyses: ceftriaxone, mannitol, and aminoglycoside levels in urine				x (during intervention)	x	
**Assessment of post-interventional clinical UTIs (primary outcome)**					x	X

^a^By phone

^b^Blood draw at 1/3/6 h post-infusion; urine culture intraoperatively

^c^Only if abnormal values at V2

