### Study intervention/allocation to blind treatment

The study will employ a pre-defined allocation table with balanced 1:1:1 to ensure equitable participant distribution, generated by the clinical research unit of the CHUV Pharmacy according to their standard process. The preparation of the study drug will be carried out by the unblinded pharmacist investigators. The intervention will consist in a single infusion over 30 min. The three treatment groups are:Amikacin (low dose) + mannitol (arm 1): aminoglycosides (amikacin 500 mg, approximately 7.5 mg/kg; potentiated with mannitol 5 g). Thus, this combination therapy of aminoglycosides and mannitol reduces toxicity by decreasing the aminoglycoside dosing (potentiation of the activity of aminoglycosides by mannitol).Amikacin (arm 2): a standard of antibiotic prophylaxis for endourological treatments (ureteroscopies, TURP, etc.). The dosage of 1000 mg is standard dosing for the average adult weight (ca. 15 mg/kg) [11, 22], a first-line treatment for urinary tract infections in Australia (*sahealth.sa.gov.au*).Ceftriaxone (arm 3): a standard of care antibiotic prophylaxis in Switzerland. In clinical practice in Switzerland, asymptomatic bacteriuria is generally treated by antibiotics as recommended by IDSA guidelines [7]. The dosage of 2 g intravenously reflects the general practice.

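### Blood pharmacokinetic parameters are promised for ceftriaxone and for each arm, but the visit schedule lists no ceftriaxone blood assay; the time origin of the draws and the label Cmax also need fixing.

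*Protocol article*

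**What the plan says.** The Statistical analysis section states: "Primary pharmacokinetic parameters in blood (Cmax, AUC, t1/2) will be calculated for mannitol, amikacin, ceftriaxone, and for each intervention arm". Study endpoints lists the matching secondary outcome as "primary pharmacokinetic parameters of mannitol and antibiotics in blood and urine samples at specified time points", without naming the antibiotics. The account of visit 1 under Study procedures/participant timeline mentions blood and urine samples for antibiotic concentrations, also without naming drugs or times.

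Table 2 (Assessments) is the only place that sets out analytes and times. Its blood row reads "Blood draw for analyses: aminoglycoside + mannitol level (AMK/Man level) at 1, 3, and 6 h after administration of drug". Its urine row reads "Urine sampling for analyses: ceftriaxone, mannitol, and aminoglycoside levels in urine". Footnote b adds "Blood draw at 1/3/6 h post-infusion; urine culture intraoperatively"; the footnote mark sits on the safety-laboratory and urine-culture rows, not on the pharmacokinetic row.

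Under Study intervention/allocation to blind treatment: "The intervention will consist in a single infusion over 30 min". Arm 1 receives amikacin with mannitol, arm 2 amikacin alone, arm 3 ceftriaxone alone.

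**The concern.** The analysis names three analytes in blood and the schedule names two. Arm 3 receives neither of the two scheduled ones, so the promise of parameters for each arm cannot be met from the listed blood row. A statistical analysis plan cannot repair this, because it cannot analyse a concentration that was never assayed.

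Two smaller matters touch the same samples. The draws are timed from administration in one line and from the infusion in another. And no draw is listed at the end of the infusion, where the concentration peaks, so the largest measured value is not the peak.

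The stakes are modest but real. Pharmacokinetics is a named secondary outcome, and the Discussion itself raises the possibility that exposure will be too short for full effect. Exposure figures that are missing in one arm, or that carry a label they do not earn, would weaken that assessment.

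**Working it through.** **Analytes, promised against scheduled.**

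| Analyte | Given in | Blood parameters promised (Statistical analysis) | Blood assay in Table 2 | Urine assay in Table 2 |
|---|---|---|---|---|
| Mannitol | arm 1 | yes | yes | yes |
| Amikacin | arms 1 and 2 | yes | yes | yes |
| Ceftriaxone | arm 3 | yes | not listed | yes |

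The table names analytes separately for blood and for urine, and ceftriaxone is absent from blood only. The number of assays needed to close the gap is 30 patients × 3 draws = 90 at most.

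**Time origin.** With a 30-min infusion, a draw 1 h after the start of the infusion falls 1 − 0.5 = 0.5 h after its end. A draw 1 h after the end falls 1.0 h after it. The two readings differ by 30 min, and both put the first sample after the peak.

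**Shortfall of the first sample.** The article states no pharmacokinetic figure, so there is none to reproduce. Assume one compartment and a constant 30-min infusion, with the peak at its end. For a sample taken d hours after the end,

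C(first sample) / C(peak) = exp(−ln 2 × d / t½).

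Half-lives are not in the article; 1 to 8 h is an assumed range.

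| Assumed t½ | d = 0.5 h (hour from start) | d = 1.0 h (hour from end) |
|---|---|---|
| 1 h | 71% | 50% |
| 2 h | 84% | 71% |
| 3 h | 89% | 79% |
| 4 h | 92% | 84% |
| 8 h | 96% | 92% |

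Example: t½ = 2 h, d = 1.0 h gives exp(−0.693 × 1/2) = 0.71. The shortfall is 4% to 29% if the hour runs from the start and 8% to 50% if it runs from the end, so 4% to 50% overall.

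**AUC.** Same model, three samples, exact tail after the last one, as a share of the true AUC to infinity for half-lives of 1 to 8 h:

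| Handling of the time before the first sample | Hour from start | Hour from end |
|---|---|---|
| Linear trapezoid from zero at time 0 | 92–98% | 72–96% |
| Back-extrapolated to time 0 as if a bolus, then trapezoid | 102–133% | 102–134% |

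The direction of the error depends on the method. The tail beyond the last sample is 1–2% of the AUC at a half-life of 1 h and 58–61% at 8 h.

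**Can the peak be recovered by back-calculation?** In one compartment, yes. In a two-compartment illustration (assumed distribution half-life 0.25 h, fast fraction 30% or 50%, terminal half-life 2, 3 or 8 h), log-linear back-extrapolation to the end of infusion recovers only 66% to 86% of the peak. Three samples, all after the peak, can hardly tell the two models apart.

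**The case against.** **The mismatch may be only a label.** The abstract, Objectives, Study endpoints and the visit 1 text all speak of antibiotics in blood in general terms, the trial is double-blind, and Table 2 restricts the draws to no arm. A word dropped from a row in a condensed article explains the gap as well as a dropped assay. This stands to the extent that a reader must not infer that ceftriaxone will never be measured in blood, or that its blood parameters are settled as unobtainable in all 30 patients. It does not remove the contradiction: the one place that lists assays disagrees with the analysis section, and the general wording elsewhere suggests that the schedule is the side in error.

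**The derivation of Cmax and AUC belongs to the analysis plan.** This also stands. A reader might infer that Cmax as planned is too low and that AUC is biased downward. The article does not say that Cmax is the highest observed value or that AUC is a plain trapezoid, and the AUC error can go either way. Only the timing of the first sample relative to the peak is established.

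**The two clocks may mean the same.** Administration can be read as the completed infusion, and footnote b is not attached to the pharmacokinetic row. This is therefore an ambiguity rather than a firm contradiction. But 1/3/6 h draws appear in no other row, and 30 min matters for a 1-h sample.

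**It is a secondary outcome in an exploratory trial.** True, and it limits the weight of the point.

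**Conclusion.** The point holds in limited form. The Statistical analysis section and Table 2 disagree on ceftriaxone in blood; followed as written, the schedule yields no blood pharmacokinetic parameter in arm 3, one of three arms. That rests on the text alone and is firm.

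The time origin of the draws is ambiguous by up to 30 min. The first sample falls 30 to 60 min after the end of infusion, so an observed maximum would understate the peak. The size, about 4% to 50%, rests on one compartment and assumed half-lives of 1 to 8 h, and the effect arises only if Cmax is taken as the highest observed value.

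The correction is worth making because it is cheap. The primary comparison of postoperative infections does not use these data and is unaffected.

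**What to change.** 1. Reconcile the analytes. Either add ceftriaxone to the 1/3/6 h blood row of Table 2, or remove ceftriaxone, and the claim to parameters for each arm, from the blood pharmacokinetic sentence. The first costs at most about 90 assays on blood already drawn, assuming sample is retained; a ceftriaxone assay is already planned for urine. The second is a text edit, at the price of having no blood exposure data for arm 3.
2. State one time origin for the three draws, start or end of infusion, use it in both the row and the footnote, and record actual infusion and sampling times. Cost: wording and two recorded times per infusion plus one per draw, if not already captured.
3. Either report the first value as the 1-h concentration, or define Cmax and AUC as model-based, using actual infusion and sampling times, and state the model assumption. Back-calculation should not be presented as exact, since three post-peak samples cannot check it. Cost: a sentence in the analysis plan and, for the second option, a small amount of modelling. A draw at the end of infusion would remove the shortfall directly, but adds a sample per patient and a change to the schedule of a trial already recruiting.
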